#### Tertiary outcome: Dementia patient lifestyle/activities

While we predict that direct effects on the caregiver will be the most likely primary and secondary outcomes, we also wish to evaluate the degree to which any changes impact the lives of dementia patients themselves. Because we are not directly enrolling or evaluating patients in the study and will not compromise their confidentiality by identifying them in any way, we will gather indirect evidence of activity changes through caregivers’ subjective reports.

Lifestyle changes in the person with dementia will be measured by asking caregivers to complete the Pleasant Event Schedule-AD (PES-AD). The PES-AD yields two subscales (Frequency of events, Pleasantness of events), and assess the frequency and pleasure the person with dementia receives from daily activities (Logsdon and Teri, 1997). The PES-AD has been shown to have good internal consistency (Cronbach’s alpha; 0.86–0.95).

### Data protection

The institution has asserted that a Data Monitoring Committee will not be needed because both interventions convey a low potential for harm. We will, nonetheless, have an internal study group that will be monitoring participants’ well-being (i.e., graduate students, psychologists, formal graduate student of psychology), and will report back to the institutional report board if any adverse events arise. Privacy information and contact preference will be stored in private internal research UCSF database. We will use a unique identification code for each participant and all coded data will be maintained in computers equipped with security programs. We will not use individual identities in any reports or publications without expressed written permission and no data will be added to medical/clinical records. The active control group will be assignment of a new, non-identifiable email account (key linking private email address) which will be only available to UCSF research team. Participants’ responses to written material will be private and recordings of participants’ interviews will be stored on a HIPAA-secure research server until transcribed, saved under deidentified file names, and be accessible only by approved research personnel (for transcription). All recording copies will be destroyed after transcriptions are performed/when the study is completed.

### Data analysis plan

The study will use mixed methods, integrating quantitative and qualitative strategies, making no assumptions about linear relationships between quantitative and qualitative data/findings (DePoy and Gitlin, 1994). These two strategies will be employed as different ways of exploring and understanding the theme in question, i.e., mindfulness and caregiver wellbeing.

Regarding quantitative measures we will first identify factors that are confounders between the two intervention groups, which may include socio-demographics, relationship to care recipients, healthcare access, socioemotional support, dementia patient diagnosis, engagement in intervention, relationship quality with facilitator, hours (weekly) spent with the person with dementia. Any variables showing significant group differences will then be considered confounds and included in the main statistical analyses. We will also check for missing data and signs of systematic response bias in self-reported responses. The main analysis will evaluate the effect of treatment group x time (t0, t1, t2). All participant outcome measures (domains: relational well-being, psychological well-being, dementia patient’s lifestyle changes), will be analyzed using generalized linear mixed models. Models will treat treatment and time points (including their interaction) as fixed effects and caregivers as random effects. We will look for a main treatment effect, a main time effect, and an interaction effect of treatment by time. All hypotheses will be individually evaluated at a nominal *p*-value of 0.05.

Semi-structured interviews will be analyzed using thematic analysis. First, grounded theory’s open coding stage will be employed, followed by axial coding and analyses (Spradley, 1979; Charmaz, 2006). We will identify meaningful themes and conceptualize our findings in relation to existing mindfulness theories and stress reactivity research. Because the first two authors are mindfulness teachers who have worked extensively with older adults, including dementia caregivers, qualitative data will be analyzed separately and jointly by the first two authors. Final synthesis of analyzed data will be obtained through continuous discussions among the research team until consensus is reached.

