### Strategies for improving adherence

Throughout the study, participation in both arms will be monitored, and retention enhanced *via* emails and calls. In the mindfulness-based intervention participants attending at least five of eight sessions will be defined as completers and will be included in the final analysis, though the number of completed sessions will be evaluated as a potential confound. To document participants’ daily mindfulness practice throughout the course, a weekly online survey will be employed accounting for home practice frequency and quality. In the active control arm, participants’ progress and skill completion can be monitored online by study staff; participants completing 75% of the material before the T1 assessment and attending at least one in-person session will be included in the final analysis, though different levels of completion will be evaluated as a potential confound.

Interventions may be discontinued at the participant’s request, with case-by-case evaluation of causative factors (e.g., death of care-recipient, acute trauma, intense amount of stress/grief, scheduling conflict). Any participant not meeting the preset participation thresholds will not be excluded from completing the remainder of the study, but their data will not be analyzed. Some attrition is expected, but with enhanced retention *via* direct contact with participants, we believe we can retain 80% of participants through the entire intervention and T1 assessment.

While we suggest a fairly broad array of assessment measures in this protocol, the overall time to complete them is ~1 h. In our two decades of experience performing observational research with caregivers of dementia patients, we have found that 1 h of questionnaires is not typically experienced as unduly burdensome for these individuals. However, individuals with more extreme current stressors could find the time demand for participation in the protocol daunting, thus they are fully informed of the demands on their effort during the informed consent process, at which time they will have the option to decline to participate.

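### Main-model covariates are chosen by significant between-arm differences, and the candidates include variables that arise after randomisation

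*Protocol article*

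**What the plan says.** In the protocol article, the Data analysis plan first looks for factors that differ between the two groups. Its list of possible factors has six kinds that can be recorded before randomisation: socio-demographics, relationship to the care recipient, healthcare access, socioemotional support, the patient's diagnosis and weekly hours together. It also has two that cannot: "engagement in intervention, relationship quality with facilitator". The selection rule follows: "Any variables showing significant group differences will then be considered confounds and included in the main statistical analyses".

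Strategies for improving adherence adds two more candidates. For the mindfulness arm, "the number of completed sessions will be evaluated as a potential confound"; for the control arm, "different levels of completion will be evaluated as a potential confound".

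The model is a generalized linear mixed model over t0, t1 and t2: "Models will treat treatment and time points (including their interaction) as fixed effects and caregivers as random effects". The main analysis is group by time, and a treatment main effect and a time main effect are also examined. Nothing in the article limits adjustment to baseline variables or makes it a sensitivity analysis.

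**The concern.** Under Recruitment, consent, and allocation to interventions, randomisation follows enrolment and baseline assessment. Engagement, the relationship with the facilitator and completion therefore come into being after allocation. They cannot confound the effect of assignment, but they can carry it. One arm has weekly live classes with two instructors; the other has a self-guided programme with two group discussions. A difference in these variables is thus plausible, and a significant one puts the variable into the model. The treatment coefficient is then no longer the effect of being assigned to mindfulness.

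For true baseline variables the fault is smaller. Among all randomised participants, differences are due to chance. A significance test ignores whether the variable predicts outcome, and it makes the final model depend on the data.

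What is at stake is the study's stated product. Sample size calculation says that the trial will establish preliminary effect sizes, and the Discussion says that it will inform larger studies. An estimate whose meaning depends on which screening tests were significant serves neither purpose well.

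**Working it through.** The document gives no figure for this rule, so there is none to reproduce.

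**Inputs from the document.** 20 per arm; 80% retention through T1, so 0.80 × 20 = 16 per arm; nominal 0.05 (taken as two-sided); three time points; a random effect for caregiver.

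**Assumed inputs.** The between-arm gap in engagement, its slope on outcome and the total effect are assumptions. All are in SD units.

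**1. One time point, covariate always included.** Let M = arm + N(0,1) and Y = 0.4·arm + 0.3·M + error.
- Total effect = 0.4 + 0.3 × 1 = 0.70.
- Effect given M = 0.40.
- Over 4,000 simulated trials the means were 0.702 and 0.399.
- Share removed = 0.30/0.70 = 43%.
- If M enters only when its own test is significant, it enters in 78% of trials and the mean estimate is 0.43.

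**2. One time point, selection rule applied.** Total effect 0.80, slopes 0.4 to 0.6, 10,000 runs per scenario. Without the mediator the estimate is 0.80 and power about 59%.

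| Engagement gap | Selected | Mean estimate | Power |
|---|---|---|---|
| 0.5 SD | 28–29% | 0.64–0.70 | 44–48% |
| 1.0 SD | 78% | 0.27–0.45 | 12–22% |
| 1.5 SD | 98–99% | −0.09 to 0.21 | 6–8% |

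**3. Three time points, random intercept, complete data.** This is closer to the protocol's model. The post-baseline total effect is 0.8, made up of 0.2 direct and 0.6 through a 1 SD gap. The expected average treatment effect over three time points is (0 + 0.8 + 0.8)/3 = 0.53. Means of 150 runs:

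| Model | Treatment × t1 | Average treatment effect |
|---|---|---|
| No mediator | 0.75 | 0.51 |
| Mediator as main effect | 0.75 | 0.11 |
| Mediator × time | 0.16 | 0.11 |

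With the parameters of step 1 (60 runs), treatment × t1 was 0.724, 0.724 and 0.434 in the same order. The first two agree because treatment-by-time is a within-person contrast. A covariate that is constant over time shifts all of a person's values equally and cancels.

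**4. False flags among true baseline variables.** With k independent variables tested at 0.05, the chance of at least one flag is 1 − 0.95^k. For k = 6 (the kinds listed) it is 1 − 0.735 = 26%. For k = 10 it is 1 − 0.599 = 40%.

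**The case against.** The strongest objection is that the stated main analysis is group by time, and the plan says only that selected variables are included. On the plainest reading they enter as main effects. Step 3 shows that, with complete data, the group-by-time contrast is then untouched. A reader might infer that the model simply adjusts away the treatment effect. The documents do not support that for the main contrast. The losses in steps 1 and 2 are single-time-point figures; for the protocol's model they illustrate the treatment main effect or a covariate-by-time form that the plan does not specify. This part of the objection stands.

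A reader might also infer that these variables are bound to enter, or that session counts are almost collinear with arm. Neither is established. The list is of possible factors, and entry depends on a test. At a 0.5 SD gap, engagement enters in fewer than a third of trials. Sessions and level of completion are arm-specific measures on different scales, to be evaluated as confounds; nothing says that they are merged or that controls are coded zero. The control arm also has facilitated discussions, so a facilitator relationship exists there, if a thinner one. Restricting the analysis to completers may narrow engagement gaps.

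That restriction has another side: imbalance in the analysed set may reflect selection as well as chance. Significance screening at about 16 per arm does not repair this.

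Finally, the study is an exploratory pilot, and adjusting for a baseline variable that is unbalanced by chance does not bias the effect as adjusting for a mediator does. Both are true. They make the baseline half minor, but do not excuse a rule that admits consequences of treatment as confounders.

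**Conclusion.** The rule is wrong as written. It treats variables that can be consequences of allocation as confounders and admits them to the main model on a significance test. The treatment main effect, which the protocol tests, is directly exposed. Treatment-by-time is exposed only if the covariate also enters by time, and the article does not say which form is meant.

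The size cannot be fixed from the documents. Under the assumptions in the check, a single-time-point effect of 0.70 SD becomes 0.40 if engagement is always included (0.43 if selected by test). In the three-time-point model the average treatment effect falls from 0.51 to 0.11, while treatment-by-time either stays at 0.75 or falls to 0.16. Other gaps and slopes give anything from a small loss to a change of sign.

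Screening true baseline variables is a lesser fault. The 26% to 40% is the chance of at least one false flag among independent tests. It does not measure bias.

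**What to change.** - Delete the significance-test rule.
- Limit main-model covariates to one or two prognostic variables measured before randomisation and named in advance, kept whatever their balance. If the care recipient's diagnosis is used, collapse it to a few groups, because the trial admits all categories of dementia.
- Use the baseline outcome once. Either keep t0 as a response and constrain the arms to be equal there, or make it a covariate with only t1 and t2 as responses. Adding it as a covariate to the present model, where t0 is already a response, would use it twice.
- Move engagement, facilitator relationship, sessions completed and level of completion to analyses labelled exploratory, and make the same change in Strategies for improving adherence.

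The cost is a change of wording and one or two degrees of freedom; a diagnosis factor with more groups would cost more.

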### Sample size calculation

Because this is a novel study and there are no published effect sizes for the impact of this mindfulness-based intervention on our various outcomes, this study will establish preliminary effect sizes for all measures. Due to the highly interpersonal nature of the mindfulness intervention, enrolling more than 20 participants per arm was impractical; however, considering expected attrition, this sample size will only be powered to detect large between-group effect sizes (i.e., 80% power to detect *r* > =0.70; 25% power to detect *r* > = 0.50).

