### Recruitment, consent, and allocation to interventions

Participants will be recruited by local advertisements and recruitment talks in the San Francisco Bay Area, online dementia caregiving groups, and by accessing an established research registry database. Recruitment is planned to continue until 40 eligible participants are enrolled (20 per intervention arm), and the approximate recruitment period is 2 months. Participants will not receive financial compensation for taking part in the study, and there will be no inducements for completing interventions. Participants deemed suitable for recruitment, will be contacted *via* email or phone with an opportunity to participate in additional eligibility screening, and to complete an online screening questionnaire to confirm eligibility. A follow-up email will include a review of study details (e.g., start date, expectations).

All screening and recruitment conversations will be completed by research personnel trained in the ethical conduct of human subjects’ research. Informed written consent will be obtained *via* interview with a trained examiner (*via* Zoom), during which the study will be clearly explained in detail, and caregivers will be able to ask questions prior to enrollment. Caregivers will also be informed that they can drop out of the study at any time. After this conversation, those agreeing to participate will be asked to formally consent to study participation. Due to current pandemic restrictions, DocuSign will be used to obtain participants’ consent signatures electronically. The amount of time expected for this consenting process is 20 min.

Next, for the baseline assessment part of the study (T0, 0 months), enrolled participants will be scheduled to participate in a 10-min semi-structured online interview *via* Zoom (see Supplementary material) and will complete a set of online surveys and performance tasks *via* Qualtrics. Those evaluations are designed to minimize possible subject fatigue, stress, and boredom. Breaks from testing will be allowed, and testing sessions may also be broken into multiple sessions. After all participants have completed enrollment and baseline assessment, they will be randomized to one of the two study arms and will then be informed *via* email of the group to which they have been assigned (see Figure 1; Table 1).

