**Figure 1 fig1:**
[figure not shown]
Planned flow of participants.

**Table 1 tab1:** Schedule of enrolment, interventions, and assessments.

Timepoint	Study period				
	Enrolment	Randomization	Intervention		Close-out
	*t_−1_*	*t_0_*	*t_1_*	*t_2_*	*t_x_*
Enrolment					
Eligibility screen	X				
Informed consent	X				
Allocation		X			
Interventions					
*MBSR adapted program*					
*GARDEN*					
Assessments					
*Primary outcome*		X	X	X	
*Secondary outcome*		X	X	X	
*Tertiary outcome*		X	X	X	

Randomization with 1:1 allocation ratio to one of the two arms will be conducted by a study investigator with no participant contact. Participants will be randomly allocated *via* a computerized random number sequence, generated *via* the R software (Team, 2014). Allocation will remain concealed from the study staff and participants during screening until randomization is completed.

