### Interventions

#### Mindfulness-based intervention (interactive program)

Caregivers allocated to this experiential group will take part in an adapted mindfulness-based stress reduction (MBSR) program, formatted as a live class led by two certified MBSR instructors *via* Zoom, where they practice and receive feedback on mindfulness skills. To maintain group cohesiveness, while maximizing study enrollment, two separate classes of 10 caregivers each will be conducted concurrently. Recognizing that caregivers report having restricted time availability, this mindfulness-based intervention will have shortened sessions (1.5 h each) compared to the traditional MBSR 2.5 h-sessions, to better accommodate caregivers’ needs. MBSR adaptations with abbreviated weekly sessions and daily time commitment have been shown to still render significant decreases in perceived stress (Klatt et al., 2008; Carmody et al., 2009; Hoppes et al., 2012). Caregivers will be trained in meditation practices, learn about mindfulness, and stress theory, and have group discussions covering topics such as dementia caregiving challenges, and grief in dementia caregiving. The program curriculum (see Table 2) extends over a period of 8 weeks, where participants are encouraged to complete home practices and review reading material between live sessions.

**Table 2 tab2:** Weekly MBSR adapted course content.

	Topic	Content
Session 1	Introduction to mindfulness; Finding Stillness	Introducing caregivers to the notion of mindfulness as a way of being, exploring their needs and expectations from their participation, setting the group environment, and defining the term of “awareness” as a fundamental pillar of mindfulness
Session 2	Perception and its relation to stress; Perception and Perspective Taking	Highlighting the importance of commitment to practices, exploring the notion of a “non-judgmental” attitude toward the participants’ handling of practice as well as challenges, introducing the exploration of different angles of perception and perspective taking, and investigating the “habits & barriers” set by our automatic responses

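### Mindfulness is taught in two live classes of ten, but the stated model has only a caregiver random effect, so any correlation within class is left out of the standard error

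*Protocol article*

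**What the plan says.** **Delivery.** In the protocol article, the section on the mindfulness-based intervention states that "two separate classes of 10 caregivers each will be conducted concurrently", with group cohesion given as a reason. Every session includes role play, group exercises or discussion. The sample size section limits enrolment on the same ground: "Due to the highly interpersonal nature of the mindfulness intervention". The active control programme is self-guided and online, with two group discussions, at weeks 4 and 8.

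**Model.** The data analysis plan makes treatment by time over t0, t1 and t2 the main analysis. It specifies: "Models will treat treatment and time points (including their interaction) as fixed effects and caregivers as random effects". It adds: "All hypotheses will be individually evaluated at a nominal *p*-value of 0.05".

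**What is absent.** Neither the model nor the sample size mentions class, clustering, an ICC or a design effect. The quality of the relationship with the facilitator is listed as a possible confounder, to be included only if the arms differ on it. That does not represent class membership.

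**Two other relevant facts.** Baseline assessment comes before randomization (recruitment section). The same two instructors co-lead each session (fidelity section).

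**The concern.** Ten caregivers who meet weekly, discuss grief and difficult communication, and practise together may come to resemble one another in their outcomes. If they do, each class contributes less independent information than ten separate people. The stated model would count all mindfulness participants as independent.

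Because baseline precedes randomization, a class effect can arise only after t0. It therefore falls on the treatment-by-time contrast, which is the main test. The caregiver random effect cannot absorb it, since that effect is separate for each person.

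The random-effects structure is stated outright, so this is not a detail left to a later analysis plan. The study is an exploratory pilot, but it tests every hypothesis at 0.05 and is meant to supply preliminary effect sizes for larger studies. Intervals that omit between-class variation would pass on more precision than the data hold.

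**Working it through.** The plan gives no ICC or design effect, so it has no figure of its own on this point to reproduce. Its power statement allows for attrition only and is not used here.

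**Inputs**
- Two mindfulness classes of 10; 20 per arm; 1:1 allocation (intervention and recruitment sections).
- Retention: "we believe we can retain 80% of participants through the entire intervention and T1 assessment" (adherence section). 0.80 × 10 = 8 per class, so 16 per arm.
- Nominal 0.05, taken as two-sided because the plan does not state sidedness.
- ICC within class: not given. Assumed 0.01, 0.05 and 0.10.
- Controls treated as independent, with equal total variance in both arms (assumptions).

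**Step 1. Design effect in the mindfulness arm:** DE = 1 + (m − 1) × ICC.

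**Step 2. Ratio of true to model variance for the arm difference.** Only one arm is clustered, so the ratio is (DE + 1)/2. The ratio of true to model standard error (SE), F, is its square root.

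**Step 3. Shortfall of the model SE:** 1 − 1/F.

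**Step 4. Actual type I error:** 2 × [1 − Φ(1.96/F)].

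| m | ICC | DE | Variance ratio | F | Model SE below true SE | Type I error |
|---|---|---|---|---|---|---|
| 8 | 0.01 | 1.07 | 1.035 | 1.017 | 1.7% | 5.4% |
| 8 | 0.05 | 1.35 | 1.175 | 1.084 | 7.7% | 7.1% |
| 8 | 0.10 | 1.70 | 1.350 | 1.162 | 13.9% | 9.2% |
| 10 | 0.01 | 1.09 | 1.045 | 1.022 | 2.2% | 5.5% |
| 10 | 0.05 | 1.45 | 1.225 | 1.107 | 9.6% | 7.7% |
| 10 | 0.10 | 1.90 | 1.450 | 1.204 | 17.0% | 10.4% |

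Simulation of an unclustered t test (200,000 runs per setting) gave 5.4%, 7.1% and 9.3% for 8 per class, and 5.4%, 7.6% and 10.4% for 10 per class.

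**Step 5. Does this carry over to change from baseline?** Let the ICC refer to post-baseline variance and let ρ be the correlation between baseline and follow-up, which is also not in the documents. With unit variance at each time, the change has variance 2(1 − ρ), so the class share of it is ICC/[2(1 − ρ)].
- ρ = 0.5: the divisor is 1, so the table is unchanged.
- ρ = 0.7: the divisor is 0.6. ICC 0.05 and 0.10 become 0.083 and 0.167, and type I error with 8 per class becomes 8.5% and 11.9%.
- ρ below 0.5: the divisor exceeds 1 and the inflation is smaller than in the table.

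The table is therefore an illustration, not a prediction for the planned three-time-point model.

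**The case against.** **The harm is conditional.** The documents give no ICC, and at 0.01 the inflation is negligible. A reader might infer that the standard errors are certainly wrong. The documents show only that the model has no place for a class effect if there is one. This stands, and the point is worded accordingly.

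**Instructors are shared.** The same two people appear to teach both classes from one curriculum. That removes instructor differences as a source of between-class variation, leaves mainly peer-group effects, and may favour the lower part of the assumed range. It does not show that the ICC is zero.

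**The calculation is not the planned test.** It is for a single time point, and the effect on the treatment-by-time contrast could be smaller or larger, as Step 5 shows. This stands.

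**Controls also meet.** They have two discussions, and attending at least one is a condition for being analysed. Treating them as independent is an assumption, though probably a minor one.

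**Effect sizes.** A reader might infer that the estimates handed to a later trial are inflated. Omitting class does not bias the point estimate; only its precision is overstated.

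**Two classes cannot support an estimated class variance.** So the documents do not support the reading that a random class effect should simply replace the stated model. What is lacking is a sensitivity analysis and a caveat.

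**Pilot status and other problems.** The exploratory aim, and many measures each tested at 0.05, make this a secondary matter. That lowers the stakes, but the planned tests and effect sizes still call for honest intervals.

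**Conclusion.** The point holds in conditional form. The design is partially nested, the model is stated without a class level, and nothing else in the protocol article corrects for it. Any positive correlation within class makes the standard error of the treatment-by-time contrast too small.

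With 8 analysed per class, the illustration ranges from negligible (ICC 0.01) to a near doubling of the nominal error rate (ICC 0.10). It rests on the assumed ICC, independent controls, equal total variance and a single-time-point contrast. The ratio F of 1.162 at ICC 0.10 might be read as a 16% understatement. It means that the true standard error exceeds the model's by 16%; the model's falls about 14% short of the true one.

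The change is worth making because it is cheap and alters the intervals that will be reported.

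**What to change.** 1. Record class membership for every mindfulness participant and show results by class.
2. Keep the treatment-by-time model and add a pre-stated sensitivity analysis to it, with a class variance in the mindfulness arm only, fixed at ICC 0.01, 0.05 and 0.10. Since baseline precedes allocation, let the class effect enter at t1 and t2.
3. Report the 95% confidence interval for the relational well-being contrasts at each ICC value.
4. State that the unadjusted intervals exclude between-class variation and that controls are treated as independent.
5. Use the sensitivity analysis to qualify the conclusion. A rule that an effect counts only if it survives a chosen ICC would be arbitrary, because the documents support no particular value.

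Cost: wider intervals in the sensitivity analysis, one more recorded variable, and slightly more analysis and reporting work. No added participants or visits are needed.
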